| Methods & procedures                 |               | 
Participants will be recruited by use of television, and the participant registrations and data collection will be by use of internet.
 
Participants who fulfil all of the inclusion criteria and none of the exclusion criteria will be included in the study (Visit 1) and undergo a 14 days non-treatment period. A sleep diary will be completed electronically every day during the whole study. At Visit 2 (Day 10) the selection criteria are once more confirmed, and the participant's ability to complete the sleep diary is assessed. If the participant still fulfils all selection criteria and has completed the sleep diary every day, he/she can be randomised to study treatment.
 
The participant will start taking the study treatment at Visit 3 (Day 15).
 
The treatment period will be 14 days upon the participant will answer questions related to overall assessment of treatment (Visit 4).
                                                                                                                                                                                                                                                                                                                                                                                                                                                                                                                                                                                                     |

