|  | Methods | 
Demographic data will be summarised by treatment group using means, minimums, medians, maximums and standard deviations for normally distributed variables and frequency counts and percents for categorical variables. This information will be used to describe the participants and compare the two groups with respect to these variables.
 
For each outcome (quality of sleep, latency to sleep onset, number of awakenings, total sleep time, energy level the previous day) we will report the proportion of participants in each group with an improvement and the risk ratio with 95% confidence intervals. In addition, the mean values will be calculated for each participant for both the baseline period and the intervention period as well as the change in mean score per participant for each of these five outcomes. The changes will be summarized by means, minimums, medians, maximums, standard deviations and the associated 95% confidence intervals.
 
Safety analyses will include tabulation of type and frequency of all adverse events. Any serious adverse events will be reported with comprehensive narratives.
 
Primary analysis
 
The primary analysis will compare the proportion of participants reporting an improvement in mean score of 0.5 for the quality of sleep, by a chi-square test. We will report the difference in proportion and the associated 95% confidence interval.
 
Secondary analyses will comprise
 
 
• Comparison of the proportion of participants reporting an improvement in mean score of 0.5 for the other four outcomes (sleep latency, number of awakenings, total sleep time, and energy level during the day) by chi-square tests
 
• Comparison of the proportion of participants with any improvement for each of the five outcomes by chi-square tests
 
• Comparison of the proportion of participants reporting improvement on the global self-assessment using two cut off points (better or much better, and any improvement) by chi-square tests
 
• Comparison of the mean changes in the five outcomes by two-sample t-tests.
 
• Comparison of the proportion of participants in each group recording one or more adverse events during the intervention compared to the run-in period by MacNamara's test and a chi-square test for the between group comparison
 
• An explorative analysis using repeated measures analysis of variance techniques in order to reveal any difference in the profile of the five endpoints during the intervention period taking into account the baseline period. This will also comprise a possibility to evaluate a time effect, e.g. to evaluate whether the effect is different after first day of treatment compared to a later day of treatment.
 
 
The confidence intervals will be reported without adjustments for multiple comparisons, and will be interpreted in the light of number of comparisons that are made
 |

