**4.3.2 Visit 2 (Day 10; Randomisation)**

- confirmation of inclusion and exclusion criteria
- assessment of sleep diary compliance
- randomisation
- shipment of study medication
- adverse events (daily registrations, sleep diary)
- concomitant medication (daily registrations, sleep diary)

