### 5.4 Duration of treatment

Participants will be treated for a maximum of two weeks.

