### 6.3 Adverse events and Serious Adverse Events

#### 6.3.1 Definitions of Adverse Events

##### Seriousness

Adverse Events (AE): any undesirable experience occurring to a participant during a clinical study, whether or not considered related to the investigational study medication(s).

All Adverse Events must be recorded in the sleep diaries

**Serious Adverse Events (SAE)** are defined as: an adverse experience that is fatal, life-threatening, disabling or which results in-patient hospitalisation or prolongation of hospitalisation, a congenital anomaly or occurrence of malignancy.

**Unexpected Adverse Event:** an experience not previously reported in the product information sheet or similar documents.

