### 6.3.2 Reporting of adverse events

As this is a clinical trial based on participant responses only, the adverse event reporting will be slightly different from other clinical trials.

The participant will report Adverse Events on a daily basis using the web-based sleep diaries. The participant will be specifically asked whether a physician is seen to evaluate the event. The primary physician may be contacted and asked to fill out a standard adverse event form. The form must be faxed within 24 hours to the study investigators, who will evaluate whether the event should be reported to the Ethics Committee and the Regulatory Authorities within 7 or 15 days, as applicable. All Serious Adverse Events will be followed up until resolution (i.e. asymptomatic, stabilisation or death).

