#### *Secondary analyses will comprise*

- Comparison of the proportion of participants reporting an improvement in mean score of 0.5 for the other four outcomes (sleep latency, number of awakenings, total sleep time, and energy level during the day) by chi-square tests
- Comparison of the proportion of participants with any improvement for each of the five outcomes by chi-square tests
- Comparison of the proportion of participants reporting improvement on the global self-assessment using two cut off points (better or much better, and any improvement) by chi-square tests
- Comparison of the mean changes in the five outcomes by two-sample t-tests.
- Comparison of the proportion of participants in each group recording one or more adverse events during the intervention compared to the run-in period by MacNamars test and a chi-square test for the between group comparison
- An explorative analysis using repeated measures analysis of variance techniques in order to reveal any difference in the profile of the five endpoints during the intervention period taking into account the baseline period. This will also comprise a possibility to evaluate a time effect, e.g. to evaluate whether the effect is different after first day of treatment compared to a later day of treatment.

In addition, we will compare the relationship between a change of 0.5, which we have defined as the minimal clinically important difference, with self-assessed improvement by testing the association of a change of  $\geq 0.5$  on each of the 5 variables in the sleep diary with self-assessed improvement for all of the participants independent of which group they were in by chi-square tests.

The P values and confidence intervals will be reported without adjustments for multiple comparisons, and will be interpreted in the light of number of comparisons that are made.

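### As most plainly read, the between-group adverse-event test leaves out the run-in event data the trial already collects, which costs sensitivity to a real excess on valerian

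*Protocol*

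**What the plan says.** Among the secondary analyses in protocol section 7.5 is a comparison of the proportion in each group recording "one or more adverse events during the intervention compared to the run-in period by MacNamars test and a chi-square test", where the chi-square test is for the comparison between groups. The statistical methods in the outline carry the same item: "recording one or more adverse events during the intervention compared to the run-in period".

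Section 6.3.1 defines an adverse event as "any undesirable experience occurring to a participant during a clinical study", related to the study drug or not. It sets no condition that the event should begin or worsen after the first dose. Section 6.3.2 adds: "The participant will report Adverse Events on a daily basis using the web-based sleep diaries". The visit schedule in 4.3 and the flow-chart show event registration before and during treatment. According to the outline, participants first "undergo a 14 days non-treatment period", and section 5.4 says "Participants will be treated for a maximum of two weeks". The two observation periods are therefore of similar length and use the same instrument.

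The descriptive part of 7.5 also plans a table of all events by kind and frequency. It does not say that new events will be separated from those already present. The protocol names no other between-group test for safety, and gives no event rate, carry-over rate or power for adverse events.

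**The concern.** A participant who notes a headache in run-in and notes it again on treatment has an event during treatment whatever the tablets do. If the chi-square test counts anyone with an event in the treatment period, such people count as events in both arms. Both proportions rise and the gap between them narrows. As long as the proportions lie below one half, the variance rises too.

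The run-in entries would identify these participants. On the plain reading they enter only the McNemar test, which compares periods within an arm and does not compare valerian with placebo. What is at stake is the ability of the one stated randomised safety comparison to show a real excess.

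**Working it through.** **Inputs from the protocol.** 250 to 275 per group (7.2), 1:1 allocation (7.3), and a Pearson chi-square test at two-sided 0.05 (7.2, stated for the primary endpoint and used here for the safety test).

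**Calibration.** The power formula (pooled variance, no continuity correction) reproduces all 16 rows of the sample-size table in 7.2. For 0.15 against 0.25, for example, it gives 250 per group and power 0.800, as printed.

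**Assumptions, because the protocol gives no rates.** Let e be the chance of a new event on treatment. Let r be the share in each arm who record a run-in complaint again on treatment, equal in both arms and independent of new events. Then

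P(any event on treatment) = r + (1 − r)e,

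and the difference between arms is (1 − r)(e_valerian − e_placebo). The shrinkage factor is algebra; its size depends on r.

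**Results, 250 per group, e = 10% placebo and 20% valerian:**

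| r | Placebo | Valerian | Difference (points) | Power |
|---|---|---|---|---|
| 0 | 10% | 20% | 10 | 88% |
| 2% | 11.8% | 21.6% | 9.8 | 84% |
| 5% | 14.5% | 24% | 9.5 | 77% |
| 10% | 19% | 28% | 9 | 66% |
| 20% | 28% | 36% | 8 | 48% |
| 30% | 37% | 44% | 7 | 36% |

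With 275 per group, power is 70% at r = 10% and 39% at r = 30%. With new events 15% against 25% and 250 per group, it falls from 80% to 61% at r = 10% and 35% at r = 30%. With 5% against 12%, it falls from 80% to 46% and 21%.

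**Does the reading matter?** A simulation took 30% with a run-in complaint, 70% of them recording it again, and new events 10% against 20%. Power was about 46% for any event on treatment (48% in a separate run), 55% for a between-group test of change from run-in, 73% when only participants without a run-in event could count, and 89% for new events only. Rejection with no true difference was near 5% in every version.

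**What stratification does.** Take 30% with a run-in complaint, 90% recording it again, and new events 10% against 20%, so r = 0.30 × 0.90 = 0.27.
- The any-event proportions are 34.3% and 41.6%, a difference of 7.3 points.
- By stratum the difference is 10 points without a run-in event and 1 point with one (91% against 92%). The weighted average is 0.7 × 10 + 0.3 × 1 = 7.3, the same.
- Unstratified variance term: 0.3795 × 0.6205 = 0.2355. Within strata: 0.7 × (0.15 × 0.85) + 0.3 × (0.915 × 0.085) = 0.1126.
- Expected z unstratified: 0.073/√(2 × 0.2355/250) = 1.68. Stratified: 0.073/√(2 × 0.1126/250) = 2.43.

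Stratification thus removes variance without changing the overall difference. Simulated power, unstratified against Cochran-Mantel-Haenszel, 250 per group:

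| Run-in complaint | Recorded again | New events | Unstratified | Stratified |
|---|---|---|---|---|
| 30% | 90% | 10% vs 20% | 40% | 69% |
| 30% | 70% | 10% vs 20% | 48% | 64% |
| 30% | 40% placebo, 60% valerian | 10% vs 15% | 69% | 79% |
| 10% | 50% | 10% vs 20% | 77% | 82% |

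**Why a new-event count should not take over.** In the third row valerian provokes recurrence. The any-event proportions are 0.3 × (1 − 0.6 × 0.9) + 0.7 × 0.1 = 20.8% and 0.3 × (1 − 0.4 × 0.85) + 0.7 × 0.15 = 30.3%. The calculated power is 68% for any event and 39% for new events only (10% against 15%).

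**The case against.** The strongest reply is that the document does not settle what the chi-square test counts. The sentence in 7.5 refers to the intervention relative to run-in and may mean a between-group test of that change. Rules for onset, worsening and matching of terms are also usual content of a statistical analysis plan, which is not shown, so their absence is no finding. Both points stand. They limit the concern to the test as this protocol words it, although the change-from-run-in reading loses power as well.

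A reader might infer that the test is biased or invalid. It is not: randomisation balances carried-over complaints in expectation, and the error rate stays at about 5%.

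A reader might also infer that the loss is large. The documents do not support that. They give neither r nor e, and 6.3.2 does not say that an ongoing complaint must be entered again. Chronic diseases are recorded separately (4.2.2). The exclusions in 3.2 remove people whose sleep is usually or always disturbed by pain or other physical symptoms. At r = 2% the loss is only 4 points of power. Nor is a doubling of new events expected: the introduction cites a review with a risk difference of −0.06 in favour of valerian, and 5.3 describes events as mild and similar to placebo.

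Finally, a reader might conclude that only new or worsened events should be compared. That count ignores treatment-provoked recurrence, as shown above. A worsening rule also needs severity for each entry; 6.3.1 defines severity grades, but neither 4.2.6 nor 6.3.2 says that the diary records them. The planned table of all events might still show a signal for a particular kind of event.

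**Conclusion.** The concern holds as a loss of efficiency, not as an error of validity. On the plainest reading, the between-group test leaves out run-in data that the trial already collects. Any carry-over that is equal in the two arms multiplies the risk difference by (1 − r). Under the assumed 10% against 20% new events with 250 per group, power falls from 88% to 77% at r = 5%, 66% at r = 10% and 36% at r = 30%. The direction follows from the algebra; the size rests wholly on assumed rates and on carry-over that treatment does not affect. Stratifying on run-in event status kept the 5% error rate and had more power in all four scenarios simulated, including the one where valerian provokes recurrence. It does not restore the full 10-point difference, but it recovers part of the lost power.

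**What to change.** In 7.5 and in the outline:

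1. State that the between-group comparison is of the proportion with any adverse event recorded during treatment, stratified on whether the participant recorded any event in run-in. Use the Cochran-Mantel-Haenszel test and report the stratified risk difference with its 95% confidence interval.
2. Add, as a supporting analysis, the proportion with an event type first recorded after the first dose. Match run-in and treatment entries while the groups are still coded a and b, as the two-step unblinding in 7.5 allows. This should not replace the any-event comparison. Use a criterion of worse severity only if the diary records severity.
3. Keep the tabulation of all events.

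The cost is a change of wording and some blinded matching of self-reported terms, which needs judgement. The stratified test needs no matching. Neither needs more participants or more data, apart from severity if that criterion is wanted and the diary lacks it.

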## 3 POPULATION

### 3.1 Inclusion criteria

1. Aged 18 –75 years, both inclusive
2. Insomnia lasting more than one month
3. PSQI score of > 5
4. Access to Internet and with own email address
5. At least 10 days of the sleep diary completed prior to randomisation

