### **4.2 Assessments and procedures**

#### **4.2.1 Overview**

Participants who fulfil all of the inclusion criteria and none of the exclusion criteria will be included in the study (Visit 1). As part of the registration of interest in the study, the participant must inform about their email address, mailing address and telephone number.

The participant will be contacted by the investigator by email and given a user name, which is the same as the user's e-mail address, and a password for the clinical trial web pages.

During the study the participant will be sent reminders by email for completion of the diary.

A structured sleep diary will be completed electronically every day during the whole study. At Visit 2 (Day 10) the selection criteria once more will be confirmed, and the participant's ability to complete the sleep diary will be assessed. If the participant still fulfils all selection criteria and has completed the sleep diary every day, he/she will be randomised to study treatment. Participants who at Day 14 still fulfil all selection criteria and have completed the sleep diary at least ten of the fourteen days will also be randomised to study treatment.

The study treatment will be shipped directly from a pharmacy to the participant, and the participant will start taking the treatment at Visit 3. The participant will confirm receipt of the treatment by entering the treatment number inscribed on the medicine box label into the Sleep Diary.

The treatment period will commence the first day that the participant enters the number of study medicine tablets that s/he took into the Sleep Diary and will last 14 days, at the end of which the participant will complete the Sleep Diary as usual plus three more questions. (Visit 4).

Participants will be asked to avoid using other medication for insomnia and to maintain their usual self-help strategies for their sleeping difficulties.

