## **7.6 Study populations**

#### *Intention-to-treat population*

Participants will be included in the primary intention-to-treat population if they have entered the randomisation code of study treatment (available to them on study treatment packs only) and have documented that they have taken the study medicine at least once with a corresponding completion of the sleep diary.

Only the intention-to-treat population will be analysed in this study.

Data for all participants will be listed, and a list of withdrawn participants, with all reasons for withdrawal, will be given. This also applies to data for those participants who - after having consented to participate - underwent screening examinations required for inclusion into the study but who - because a criterion for exclusion was met or for other reasons - were not included in the study.

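### The exploratory nightly profile analysis is named as repeated measures ANOVA, whose complete-row form would drop participants with a missed treatment-night diary; naming a mixed model is a minor, cheap improvement

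*Protocol*

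**What the plan says.** Among the secondary analyses, Section 7.5 (repeated in the Protocol Outline) lists "An explorative analysis using repeated measures analysis of variance techniques in order to reveal any difference in the profile of the five endpoints". The profile is the one "during the intervention period taking into account the baseline period", and the analysis should also be able to show "whether the effect is different after first day of treatment compared to a later day of treatment". No covariance structure, sphericity correction or rule for missed nights is given, and the text does not say in what form the baseline enters.

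Other sections show that the diary will have gaps:

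- Section 3.1 requires "At least 10 days of the sleep diary completed prior to randomisation".
- Section 4.2.1 randomises at Day 10 a participant who "has completed the sleep diary every day, he/she will be randomised to study treatment". It also takes those at Day 14 who "have completed the sleep diary at least ten of the fourteen days will also be randomised to study treatment", so up to four run-in nights may be missing.
- Section 3.4 provides for participants who stop filling in the diary, and Section 4.2.6 for daily reminders to those who have not completed it.

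Section 7.6 includes participants who have entered the treatment code and "have documented that they have taken the study medicine at least once with a corresponding completion of the sleep diary". It makes this intention-to-treat population the only one analysed, and Section 7.5 puts all analyses on that basis. Section 7.5 also forms a mean per participant for the baseline period and for the intervention period.

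**The concern.** The analysis population needs one treated night with a diary entry, whereas a complete-row repeated measures ANOVA needs a score on every night that is a repeated level. Run in that form, the analysis would cover only participants with a full treatment diary. That is a smaller and more diligent group than the intention-to-treat population. The other effectiveness comparisons based on the diary do not share the problem, because they use period means that can be formed despite gaps.

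There is a second, separate issue. Nightly scores from one person are likely to be serially correlated. The univariate form of the group-by-time test assumes sphericity, and without a correction it rejects too often when that fails.

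At stake is the only listed analysis that addresses time course, for five endpoints. The result could rest on a selected subset and, if the univariate test is used uncorrected, on P values that are somewhat too small.

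**Working it through.** **Inputs.** There are 14 treatment nights (Section 4.2.1) and about 250-275 participants per group (Section 7.2). The protocol gives no missed-night rate *m* and no night-to-night correlation, so both are assumed and shown over a range.

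**The plan's own figure.** The protocol states no number for this analysis. The group size it would start from does reproduce. For 0.15 against 0.25, two-sided 0.05 and 80% power:

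n = [1.960 × √(2 × 0.20 × 0.80) + 0.842 × √(0.15 × 0.85 + 0.25 × 0.75)]² / 0.10² = 250 per group, as tabulated. The other 15 rows of the table reproduce too.

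**Share with complete rows, treatment nights only.** If nights are missed independently, the share with all 14 nights is (1 − m)¹⁴.

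| Assumed m | (1 − m)¹⁴ | Of 250-275 per group |
|---|---|---|
| 1% | 87% | 217-239 |
| 2% | 75% | 188-207 |
| 5% | 49% | 122-134 |
| 10% | 23% | 57-63 |

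If misses cluster in some people, fewer are lost. With person-specific miss rates drawn from a beta distribution (parameters summing to 5), the share with all 14 nights is 87%, 70% or 48% at mean rates of 2%, 5% or 10%.

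**Do run-in gaps matter?** That depends on how the baseline enters. In a simulation of 500 randomised participants with independent misses, Day-14 entrants were retained as follows:

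| Assumed m | Day-14 entrants | Kept: 14 treatment nights, baseline as a mean | Kept: all 28 nights as repeated levels |
|---|---|---|---|
| 2% | 77 | 59 | 0 |
| 5% | 200 | 95 | 0 |
| 10% | 326 | 90 | 0 |

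With a baseline mean, run-in gaps remove nobody, and Day-14 entrants are lost only for missed treatment nights. With all 28 nights as levels, every one of them is lost. The overall share with complete rows, among those randomised, then falls to 57%, 24% or 5%.

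**Sphericity.** The uncorrected group-by-time F test was simulated over 14 nights with 250 per group and AR(1) nightly residuals. Two separate simulations gave type I errors of 6.5% and 6.2% at a residual correlation of 0.4, and 9.6% and 9.0% at 0.6, against a nominal 5%. At 0.2 the inflation was negligible (5.4-5.6%). A Greenhouse-Geisser correction brought the error back to about 4-5%.

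**With a mixed model.** A likelihood-based model on recorded nights keeps every intention-to-treat participant with at least one treatment-period diary entry, that is, up to the full 250-275 per group.

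**The case against.** The strongest reply is that the protocol names a family of techniques and not the complete-row version. The wording can cover a mixed model. Covariance structure, sphericity correction and handling of missed nights are commonly left to a statistical analysis plan, which is not at hand. The analysis is labelled exploratory, is not tied to any objective in Section 2, and has P values reported without multiplicity adjustment and read in that light. This stands, and it is why the point is minor. It does not remove the point, because the same wording equally permits the classical form, and the two forms analyse different sets of people.

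Four stronger conclusions that a reader might draw are not supported:

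- *All Day-14 entrants will be discarded.* This needs the 14 run-in nights to be repeated levels. The text profiles the intervention period and only takes the baseline into account, and Section 7.5 already forms a baseline mean that tolerates gaps.
- *The plan contradicts its intention-to-treat rule.* It would do so only if complete-row deletion were applied, and the protocol does not say that it will be.
- *Most of the precision is lost.* Even with all 28 nights required, complete-case standard errors are only 1.11 and 1.24 times those from all recorded nights when misses cluster at 2% and 5%, and 1.34 times for independent misses at 2%. The ratio reaches 4.26 only with 28 nights, 10% missed and full independence.
- *Both defects necessarily occur together.* The multivariate form needs complete rows but does not assume sphericity. A long-format univariate analysis assumes sphericity but can run with gaps.

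Independence of misses is also doubtful, since participants are selected on diary completion and reminded daily. The figures for independent misses are therefore better read as the pessimistic end.

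**Conclusion.** The point holds as a minor, conditional improvement. If the exploratory analysis were run as a complete-row ANOVA on the treatment nights, it would keep about 75%, 49% or 23% of participants at assumed independent miss rates of 2%, 5% or 10%, and about 87%, 70% or 48% under the clustering assumed above. That would not be the population Section 7.6 commits to. Run-in gaps add to the loss only if run-in nights are repeated levels. If a univariate test were used without correction, its type I error would be roughly 6-10% for an assumed residual correlation of 0.4-0.6. All these sizes rest on assumed rates and correlations. The primary chi-square test, the comparisons based on period means and the sample size are untouched.

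**What to change.** In Section 7.5 and the Protocol Outline, replace the reference to repeated measures ANOVA techniques with a likelihood-based linear mixed model on all recorded treatment-period nightly scores. Specify:

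- group, night and group-by-night as fixed effects;
- the participant's baseline mean as covariate, which also settles how the baseline enters;
- a covariance structure, stated in advance, that allows serial correlation;
- inclusion of every intention-to-treat participant with at least one treatment-period diary entry.

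The cost is about one sentence of text and slightly more modelling work. The downside is that the covariance structure must be chosen beforehand and that missing nights are assumed missing at random. That assumption is still weaker than what a complete-case analysis needs.
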